#### Development of Gaming Education Program

The gaming education program was developed based on previous study [19,20,22]. The authors modified the study outline based on the participants and purpose of this study. The gaming educational program in this study comprises 3 primary components, as outlined in Table 1. The sequence of the short film (undesirable communication with people living with dementia), lecture, N-impro gaming, and the desirable communication with people living with dementia scenarios is determined based on insights from previous studies. The gaming education program is designed to be conducted within 90 minutes. The 3 primary components of the gaming education program are as follows.

**Table 1 table1:** Overview of the gaming educational program.

The content of the education program			Time
**Introduction of the study**			
	Principal investigator explained the overall of study and content of inform	5 min	
**Pretest**			
	Participants will receive a QR code providing access to information regarding Informed Consent and the online questionnaire.	10 min	
**Short film (Undesirable communication with people living with dementia scenario)**			
	Observing a narrative featuring a woman people living with dementia, participants reflect on her background and the reactions of those around her.	10 min	
**Lecture**			
	The lecture consists of dementia, treatment of people living with dementia, person-centered care, and social support. The lecture included questions and answers.	25 min	
**N-impro gaming**			
	In the gaming setting, students will participate as a group alongside a facilitator. The game is structured with components such as “situation cards,” “answer cards,” and “point cards.” All groups will be provided with identical sets of situation cards.	20 min	
**Short film (Desirable communication with people living with dementia scenario)**			
	Participants identify differences in the emotional experiences of people living with dementia and the reactions of individuals in their immediate surroundings between the two given scenarios.	10 min	
**Posttest**			
	Participants will be issued a QR code to access the online posttest. In addition, there will be a designated space for participants to provide free-form comments expressing their opinions and feedback on the gaming education program.	10 min	

#### Short Drama Portraying Undesirable and Desirable Scenarios

Participants will view a short drama depicting an older woman who may be experiencing dementia. The narrative explores her life history, values, and interactions with family, friends, and community members. In total, 2 parallel scenarios are presented, showcasing both desirable and undesirable communication methods. This contrast enables the participants to subjectively experience the emotional responses of the main character to different types of communication; thus, the participants can naturally learn the appropriate method of communicating with people living with dementia. The scenario of the short drama was created based on interviews with people living with dementia and their families, a review of scholarly articles, and consultations with experts in dementia care. The research team translated a Japanese drama into Indonesian and added subtitles. The drama was projected onto a screen, akin to the setting of a movie theater.

#### A Lecture About Dementia

Lectures form the foundational framework of this educational program, which is based on the established curriculum for dementia-related health education. Furthermore, the contents of these lectures have been fashioned from the condensed dementia supporter training program in Japan [23,24]. These include the definition of dementia, diagnostic procedures, the various types of dementia, underlying causes, symptoms, treatment and prevention strategies, person-centered care and social support for people living with dementia, and the point of nursing care and how to support the people living with dementia.

Japanese researchers will curate the content outline, followed by their Indonesian counterparts, who will generate the presentation slides and conduct the lectures. A proficient senior lecturer will deliver the courses. The lessons will be systematically recorded and subsequently projected onto screens during class sessions to ensure uniformity across all instructional content in the various class settings.

#### N-Impro (Gaming Tool)

We developed the gaming tool based on the methodology of a disaster education program [25] and modified it to discuss dilemmas that can occur in a convenience store [19]. The game comprises “situation cards,” “answer cards,” and “point cards.” The situation cards present a 3-part scenario: (1) assigning a role to the participant (eg, you are a convenience store manager), (2) describing a relevant dilemma, and (3) prompting the participant to choose a course of action (yes or no). We developed eleven situation cards, each depicting a unique dilemma based on episodes from the interviews. For instance, the following situation card was created:

You are a convenience store manager. You suspect a customer has dementia and are concerned for his well-being. You have previously consulted a welfare volunteer about the customer; however, she said she can do nothing until the name or address of the customer is identified. The customer visits your store irregularly, and you are unable to learn his name because of his unintelligible.

Other situation cards were similarly crafted to reflect various dilemmas. The N-impro cards are available in Japanese and English. The professional translator translated into Indonesian (Multimedia Appendix 1).

The N-impro game will be played for about 25 minutes during the third session. The research team will provide 6-7 cards with the same scenario and order for each group. Each N-impro game group will consist of 7-8 students with 1 facilitator. The facilitators are teachers in the faculty of health care. The facilitator has undergone 2 training sessions. In the first session, training was conducted by a Japanese team, which included video demonstrations of the N-impro game and slides explaining the game rules. Then, in the second session, the research PI in Indonesia completed offline training for all facilitators to present the game rules and further discuss and role play the N-impro game.

### Data Collection

Data will be collected from November 2023 to March 2024 through an online questionnaire. Participants will be informed to prepare a mobile phone or personal computer before joining the class. For the online questionnaire, participants need to access the form, enter the required information, complete the questionnaire, and submit the form. Participants do not need to log into their Google accounts to access the link. They will only provide the new ID number at the beginning of the form. The link to the questionnaire will be shared through a QR code displayed on the classroom screen.

### Measurement

This study assesses the pre- and posttest outcomes of a gaming-education program focused on dementia. We aim to measure the effectiveness of the education program by evaluating attitudes toward people living with dementia, intentions to assist people living with dementia, knowledge of dementia, and stigma associated with people living with dementia. This study hypothesizes that a gaming-based education program will foster positive attitudes toward people living with dementia and an intention to help people living with dementia. Furthermore, we anticipate that the knowledge gained from the lectures and discussions during the gaming education will enhance the confidence of health care students in caring for people living with dementia.

This study uses the model by Lane and Yu, which encompasses 3 primary concepts contributing to dementia-friendly communities: knowledge of dementia, attitudes toward people living with dementia, and the intention to assist people living with dementia [26]. The model is underpinned by 2 theories: first, an increase in dementia knowledge is directly linked to a high intention to help people living with dementia, and second, attitude is an intermediary factor between knowledge and intention, influencing the formation of intention and potentially enhancing tangible supportive actions. Therefore, according to this model, improvements in both knowledge and attitude should strengthen the intention to assist.

The questionnaire used in this research is in Indonesian (Bahasa). The questionnaire was originally in English and Japanese. We performed a forward and backward translation into Indonesian using the standard method [27]. The translation process involves 2 stages. First, a health care professional who is fluent in both Japanese and Indonesian, has expertise in dementia, and possesses knowledge of Japanese and Indonesian culture performs an initial forward translation. Second, a professional translator who is proficient in Japanese-Indonesian language performs the back translation. Afterward, the Japanese research team validated the translations. Subsequently, we sought input from an Indonesian lecturer, an associate professor in the Department of Japanese Studies, Department of Gerontological Home Care and Long-term Care Nursing, University of Tokyo to ensure the fluency and uniqueness of sentences in Indonesian. The following are the measurements.

#### Primary Outcomes: Attitudes Toward People Living With Dementia

The primary focus of this study is the attitude toward people living with dementia, as it is intrinsically linked to the concept of attitude. The main objective of education aimed at fostering a dementia-friendly community is to enhance attitude. Attitude, as a concept, is a mental and neural state molded by experience, which influences the responses of individuals to various objects and situations and exerts a directive or dynamic impact on their behavior [28,29]. Consequently, numerous previous studies have used attitude as the primary outcome in educational research [22,30-32].

People’s perceptions of people living with dementia are related to stigma. Stigma is a societal phenomenon characterized by others perceiving an individual as deviating from the norm [33]. There are significant obstacles to creating communities that are supportive of people living with dementia, including stigma and social isolation. Stigma can impede the provision of care and support, frequently manifesting in behaviors such as excluding people living with dementia from health care [34,35]. Stigma can significantly influence the attitudes and behaviors of health care students. Therefore, measuring attitudes toward people living with dementia is important among health care services and students, as it relates to people’s perceptions of people living with dementia.

Attitudes toward people living with dementia were assessed using a 14-item measurement tool developed using information from previous research. This tool uses a 4-point Likert scale, ranging from 1 (disagree) to 4 (agree), and comprises 4 subscales: tolerance (5 items), refusal (4 items), feeling of distance (3 items), and affinity (2 items). The total score ranged from 14 to 56, with high scores indicating favorable attitudes. Tolerance was assessed with the statement, “I am open to having more interactions with people living with dementia in my daily life.” Refusal was measured by “I prefer to minimize interactions with people living with dementia as much as possible.” The feeling of distance was gauged with “If a family member were to develop dementia, I would be concerned about what people around me would think.” Affinity was evaluated by “If someone with dementia requires assistance, I would readily offer help.”

#### Secondary Outcomes

##### Knowledge of Dementia

Knowledge of dementia will be measured using the 15-item Dementia-Related Knowledge Scale developed by Kim and Kuroda [36], which assesses the knowledge of dementia: its symptoms, treatments, and diagnosis. This scale will require respondents to provide answers using a 3-point Likert scale ranging from agree, disagree, and don’t know. The author will calculate the total dementia knowledge score, with a high score indicating a high level of knowledge about dementia.

##### Ageism Among People Living With Dementia

Ageism is stereotyping, prejudice, and discrimination against individuals based on their age [37]. Dementia is often associated with advanced age. To develop dementia-friendly services by health care professionals, it is crucial to investigate the prevalence of ageism among people living with dementia. Thus, we will use the Fraboni’s Scale of Ageism (FSA) short version to assess the level of ageism among people living with dementia [38,39]. The FSA short version comprises 19 items that measure negative opinions toward older people using a Likert scale (1=strongly disagree, 2=disagree, 3=agree, and 4=strongly agree). Items that represent positive opinions toward older adults have reversed scoring (items 13-16). The possible FSA scores ranged from 19 to 76, with the high scores indicating high levels of ageism.

##### Intention for Helping Behaviors Toward People Living With Dementia

Based on previous research, methods aimed at raising awareness about dementia and providing education to individuals can enhance the probability of individuals engaging in supportive actions through 2 mechanisms. Individuals tend to develop favorable attitudes toward people living with dementia, and they improve their capacity to recognize signs indicating a need for assistance [40]. Therefore, the intention to help will be measured using 4 vignettes derived from the previous study. The vignettes describe situations in which people living with dementia may require assistance. For example, consider a scenario where you are a clerk in a supermarket. An older woman, a regular customer, arrived this morning to buy 2 bunches of bananas; however, it is now evening, and she has returned to purchase 2 more bunches. She also visited the supermarket twice yesterday for bananas and is appropriately dressed. Participants will read each vignette and, for each one, will be asked to indicate their answer to the item “You will help her.” The intention to help will be scored using a Likert scale (1=strongly disagree, 2=disagree, 3=agree, and 4=strongly agree). A high score indicates a high intention to help people living with dementia.

##### Demographic Data

Demographic information will be collected, including participants’ age, sex, affiliation, relationship to people living with dementia, experience in assisting and caring for elderly individuals (including people living with dementia), and history of attending dementia-related lectures, whether through a formal course or a dementia-focused organization.

### Data Analysis

Statistical analyses will be performed as follows: initially, descriptive analyses will be conducted to outline the characteristics of the participants. Subsequently, we will evaluate changes in total and subscale scores for attitudes toward people living with dementia, intention to help people living with dementia, knowledge of dementia, and stigma associated with people living with dementia before and after the program using paired *t* tests and the Wilcoxon rank sum test. To determine the effectiveness of the program, we will calculate effect sizes using Cohen *d*, classifying differences between pre- and postprogram scores as small (*d*=0.2), medium (*d*=0.5), or large (*d*=0.8). We will set the threshold for statistical significance at *P*<.05 (2-tailed). The statistical analysis will be conducted using IBM SPSS Statistics (version 26.0).

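### The plan tests five attitude scores with two tests each at unadjusted P<.05 and does not say which score or test decides the primary claim

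*Protocol article*

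**What the plan says.** The protocol article gives attitude the leading place. Under the heading "Primary Outcomes: Attitudes Toward People Living With Dementia" it states that "The primary focus of this study is the attitude toward people living with dementia". The instrument "comprises 4 subscales: tolerance (5 items), refusal (4 items), feeling of distance (3 items), and affinity (2 items", and its total runs from 14 to 56. Knowledge, ageism and intention to help are described under Secondary Outcomes. Knowledge, for example, is reduced to one total: "The author will calculate the total dementia knowledge score".

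The Data Analysis section then puts everything on one footing. It says "we will evaluate changes in total and subscale scores for attitudes toward people living with dementia" and goes on to "intention to help people living with dementia, knowledge of dementia, and stigma associated with people living with dementia before and after the program". The methods are paired t "tests and the Wilcoxon rank sum test". One threshold covers all of it: "We will set the threshold for statistical significance at" P<.05, two-tailed. The section mentions no adjustment and gives no rule for choosing between the attitude total and its subscales, or between the two tests.

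Two further sentences widen the basis for a claim. The Measurement section says that effectiveness will be judged on all four outcomes. Data Analysis says that Cohen d will be used to determine effectiveness, without naming the score.

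**The concern.** A single primary test at 5% two-sided carries a 2.5% risk of a false improvement. That protection holds only if the plan says in advance which test it is. Here a statement that attitudes improved could rest on the total or on any of four subscales, by either of two tests. A statement that the program is effective could rest on at least eight scores. The 5% threshold then no longer describes the risk attached to the claim.

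This matters more than usual because the study has no control group, as its Limitations section acknowledges. The pre-post P value carries the whole inference, and the decision rule is one safeguard that can be fixed without touching the design.

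**Working it through.** The article states no overall error rate, so the only figure of its own to compare with is the 5% threshold.

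**Inputs from the article**
- Attitude scores: 1 total + 4 subscales = 5 (Primary Outcomes section).
- Other scores: knowledge, ageism (called stigma in Data Analysis) and intention = at least 3, so at least 5 + 3 = 8 in all.
- Threshold: 0.05 two-tailed per test, which is 0.025 in the favourable direction.
- Sample size: 68 (Participants and Settings).

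**Assumption, not in the article:** the correlation between changes in different scores, taken from 0 to 0.7.

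**Step 1. One test of the attitude total.** The chance of a significant result is 5%, and of a false improvement 2.5%.

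**Step 2. Simple arithmetic for independent scores, one test each.**
- Five attitude scores, false improvement: 1 − 0.975^5 = 11.9%.
- Eight scores, false improvement: 1 − 0.975^8 = 18.3%.
- Eight scores, either direction: 1 − 0.95^8 = 33.7%.

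These are only rough, because the total is made of the same 14 items as its subscales and cannot be independent of them.

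**Step 3. Simulation with no true change.** n = 68 and 10,000 replicates. Every score is oriented so that a rise is favourable, and the attitude total is built from its four subscales weighted 5, 4, 3 and 2. The signed-rank test stands in as the paired form of the Wilcoxon test.

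| Correlation | Total, t only: improvement | Total, either test: improvement | Five attitude scores, t only: improvement | Five attitude scores, either test: improvement | Eight scores, either test: improvement | Eight scores, either test: any direction |
|---|---|---|---|---|---|---|
| 0 | 2.6% | 3.2% | 10.4% | 12.1% | 20.0% | 36.5% |
| 0.3 | 2.8% | 3.2% | 9.3% | 11.0% | 16.4% | 32.0% |
| 0.5 | 2.5% | 3.0% | 8.6% | 10.0% | 13.8% | 27.1% |
| 0.7 | 2.5% | 3.0% | 6.6% | 8.0% | 10.9% | 21.5% |

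A repeat with other random numbers gave 7.4% to 12.5% for the five attitude scores and 10.2% to 20.3% for the eight (either test, improvement). Allowing for such variation between runs, the rounded ranges are 7–13%, 10–20% and, for either direction, 20–38%.

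**Step 4. Where the inflation comes from.** At correlation 0, adding the second test to the total raises the rate from 2.6% to 3.2%, or 0.6 points. Moving from one score to five with the t test alone raises it from 2.6% to 10.4%, or 7.8 points. The number of scores drives the result.

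**Step 5. The Wilcoxon test as named.** The rank sum test is for independent samples. On pre-post data its own error rate falls below 1% at a pre-post correlation of 0.5 or more (also an assumption). As written it therefore adds almost nothing, and it is not the paired test that the design calls for.

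**The case against.** The strongest reply is that the plan is loose but not silent. Attitude is named primary and the rest secondary, so a false result on knowledge cannot show that attitudes improved. Only the attitude total is given a range and a direction. The sample size rests on a matched-pair t test, which hints that this test leads. The conditions for using t or Wilcoxon, and the handling of secondary outcomes, are often left to an analysis plan that is not shown here.

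Much of this stands. It makes the five-score attitude family the right basis for the primary claim, and it makes adjustment of the secondary outcomes a matter of preference. It does not close the gap. Data Analysis does state an analysis, and it puts total and subscales, and both tests, under one threshold. The sample size section does not say which score its effect size refers to.

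A reader might infer a stronger point: that the chance of a false improvement is one in four to more than one in three. The documents do not support that. The threshold is two-tailed, so figures of that size count false worsenings as well; the favourable direction alone is about half. They also pool secondary outcomes with the primary one, and they fall to about 20% at a correlation of 0.7. A reader might also infer that the score and test will be picked after the results are seen. The article leaves room for that but does not say it.

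**Conclusion.** The concern holds in this form: the primary claim has no named deciding score or test. The risk of a false attitude improvement on at least one of five scores is about 7–13%, roughly three to five times the 2.5% of a single test (7/2.5 = 2.8; 13/2.5 = 5.2). If any of the eight scores may support effectiveness, as the Measurement section allows, the risk is about 10–20%.

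The ranges rest on the assumed correlation of 0.7 to 0, on no true change in any score, on approximately normal changes, and on reading the Wilcoxon test in its paired form. The qualitative conclusion depends on none of these beyond the scores not being near-duplicates of one another. It is a cheap improvement rather than a fatal flaw.

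**What to change.** In Data Analysis, state that effectiveness on the primary outcome is decided only by the two-sided 5% paired t test of the 14–56 attitude total. Name the Wilcoxon signed-rank test, in place of the rank sum test, as a sensitivity analysis. Report the four subscales descriptively with confidence intervals. Label knowledge, ageism and intention as secondary results that cannot by themselves support a claim of effectiveness, and bring the Measurement sentence on effectiveness into line.

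The cost is a few sentences and no power for the primary test. The small downside is that a significant subscale or secondary result alone can no longer carry the main claim. The article's schedule puts the end of analysis at May 2024, before its publication in September 2024. If the results had already been seen, the report should say when the rule was set and mark all other tests as secondary or exploratory. If a fuller plan already names the total and the test, the article's wording need only be aligned with it.

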## Methods

### Study Design

This study will use a single-arm pre-post design to assess the effectiveness of gaming-based dementia educational programs for health care students. The study will be conducted in collaboration with the Faculty of Health at an Indonesian University. The programs will be integrated into courses related to dementia care, such as the Gerontological Nursing Care course, the Psychiatric Nursing course, and the Health Assessment course. Participation in the study is open to all students in these classes. However, there will be no penalties for students who choose not to participate. The study will continue until participant inclusion is completed, which is anticipated to be around March 2024.

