### Participants and Settings

Participants in this study will be health care students at an Indonesian University. For this study, we will invite nursing and public health students. A participant must meet the following inclusion criteria: they must be a health care student enrolled in the semester for which we have designated the course for the implementation of this educational program. For instance, nursing students at Airlangga University will be selected from those in the fifth semester. While public health students are in the sixth semester, both are third-year grade health care students with class topics related to dementia. Prospective participants will be assigned a new ID number to ensure their student ID numbers remain confidential. The sample size was calculated using a power analysis for differences between two dependent means (matched pairs). The total sample size is 68 health care students with an effect size of *d*=0.5 (Reference from N-impro study: *d*=0.5, α=0.05, power=0.80). In conducting a matched pair *t* test analysis, this study will collect sufficient data from the participants; the sample size will exceed the calculated sample size.

This study will be conducted at Indonesian universities with health-based faculties. Health education activities will be implemented in various classrooms within the university. Each classroom will accommodate approximately 50 participants and will be equipped with chairs and tables to facilitate discussion. The classrooms will be divided into 4 parts, each comprising up to 10 chairs.

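### The before/after comparison in the same students names the Wilcoxon rank sum test, which is for independent groups; run as written, its P values are invalid

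*Protocol article*

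**What the plan says.** Under Study Design, the protocol article states: "This study will use a single-arm pre-post design to assess the effectiveness of gaming-based dementia educational programs for health care students". Under Participants and Settings, the sample size rests on a "power analysis for differences between two dependent means (matched pairs"), and the text then refers to a matched-pair t test. The stated size follows: "The total sample size is 68 health care students with an effect size of" d = 0.5, with the parameters given as "0.5, α=0.05, power=0.80".

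Table 1 schedules a pretest and a posttest within the same session. On the questionnaire form, Data Collection says of participants: "They will only provide the new ID number at the beginning of the form". That identifier allows a student's two records to be linked.

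Under Data Analysis, "we will evaluate changes in total and subscale scores for attitudes toward people living with dementia" and for the other outcomes, before against after the program, using paired t "tests and the Wilcoxon rank sum test". Significance is two-tailed at P < .05. The signed-rank test is not named anywhere in the article.

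**The concern.** The two Wilcoxon tests have similar names but answer different questions. The rank sum test pools two unrelated samples and compares their ranks, with a standard error that assumes independence between the samples. The signed-rank test ranks the within-person differences and is the nonparametric counterpart of the paired t test. The design, the sample-size basis and the t test in this plan are all paired; the nonparametric test named beside them is not.

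The same student answering the same scale twice in one session will very probably give positively correlated scores. The rank sum standard error is then too large and the P value too high. A real change could be reported as non-significant. The two tests in the same sentence could also disagree only because one ignores the pairing, and the article gives no rule for which then prevails. A nonparametric result is most likely to be looked to for short ordinal subscales, such as the 2-item affinity and 3-item distance subscales, which Data Analysis includes among the scores to be tested.

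**Working it through.** **Inputs from the protocol article**
- Single-arm pre-post design (Study Design).
- N = 68, d = 0.5, α = 0.05, power 0.80, matched pairs (Participants and Settings).
- Two-sided testing at 0.05 (Data Analysis).
- Attitude total from 14 to 56 (Primary Outcomes).

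**Assumed, because the article does not give them**
- Pre-post correlation ρ, varied from 0 to 0.8.
- Normal scores with mean 40 and SD 5, rounded to the 14–56 scale, for the simulation.

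**Step 1: the plan's own figure.** Power of the two-sided paired t test comes from the noncentral t distribution with n − 1 degrees of freedom and noncentrality d√n.
- n = 34: noncentrality 0.5 × √34 = 2.92, power 0.808. This is the smallest n that reaches 0.80.
- n = 68: noncentrality 0.5 × √68 = 4.12, power 0.982.

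The stated 68 therefore does not reproduce as a number of pairs. It equals 2 × 34, as if observations had been counted rather than students, though that is an inference. This is a separate matter and the present point does not depend on it. I show both 34 pairs (what the stated inputs require) and 68 (what the plan states).

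**Step 2: why the rank sum test misstates the error rate.** With no true change, the real variance of the rank difference is about (1 − ρs) times the variance the test assumes, where ρs is the rank correlation. For normal scores ρs = (6/π)·arcsin(ρ/2). The test rejects when its z exceeds 1.96, so the actual size is about P(|Z| > 1.96/√(1 − ρs)).

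| ρ | ρs | 1.96/√(1 − ρs) | approximate true size |
|---|---|---|---|
| 0 | 0 | 1.96 | 0.050 |
| 0.3 | 0.288 | 2.32 | 0.020 |
| 0.5 | 0.483 | 2.72 | 0.006 |
| 0.7 | 0.683 | 3.48 | 0.0005 |

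**Step 3: simulation.** 10,000 data sets per setting, both tests two-sided at 0.05 with tie correction. The effect is fixed at 0.5 SD of the within-student difference, the scale on which the sample size is stated.

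| ρ | size, rank sum, n = 68 | power, rank sum, n = 68 | power, signed-rank, n = 68 | power, rank sum, n = 34 | power, signed-rank, n = 34 |
|---|---|---|---|---|---|
| 0 | 0.051 | 0.98 | 0.98 | 0.80 | 0.79 |
| 0.3 | 0.021 | 0.95 | 0.98 | 0.67 | 0.79 |
| 0.5 | 0.007 | 0.89 | 0.98 | 0.52 | 0.80 |
| 0.7 | 0.0004 | 0.66 | 0.98 | 0.24 | 0.78 |
| 0.8 | 0.0001 | 0.37 | 0.98 | 0.09 | 0.79 |

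The signed-rank test has a type I error between 0.047 and 0.053 at every correlation and both sample sizes. The simulated sizes agree with the approximation in Step 2. A separate simulation with unrounded normal scores gave close agreement: at n = 68 and ρ = 0.5, 0.6 and 0.7, rank sum size was 0.0073, 0.0032 and 0.0005, and power 0.886, 0.807 and 0.656.

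Neither simulation models a 2-item subscale, so these figures describe the total score and not the short subscales.

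**The case against.** The strongest reply is that this is a slip of the pen. The sentence speaks of changes before and after the program, couples the test with paired t tests, and follows a matched-pairs sample size. The authors may well have meant signed-rank and may have run it. That is plausible, but the text still names an independent-samples test. An analyst following it would choose the wrong procedure, and a reader could not tell which one produced a reported P value.

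Second, the harm is limited. The test tied to the sample size is the paired t test, which is correctly named. With positive correlation the error costs power and produces no excess of false positives. All of this stands, and it bears on how much damage follows, not on whether the named test is wrong.

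Third, the size depends on a correlation the article does not give. At ρ = 0 nothing is lost, and at 0.3 the loss at n = 68 is small (0.95 against 0.98). At the stated 68 students and ρ = 0.5, rank sum power of 0.89 still exceeds the 0.80 target; it falls below the target by ρ = 0.7. The n = 34 columns show what happens at the number of pairs the stated inputs need; the plan itself intends to exceed 68. These are fair limits on the size. They do not rescue the test, whose nominal level holds only if a student's two answers are uncorrelated.

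Finally, the article does not say when the nonparametric test will be relied on, so its importance for the subscales is a reasonable expectation and not something the plan states.

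**Conclusion.** The concern holds. The named test does not fit the paired design, and the article describes no other comparison for which it could be meant. This is a wrong statement in the text, not a detail left to an analysis plan.

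Run as written, the nonparametric P values are invalid at any positive pre-post correlation, and always in the conservative direction. For correlations of 0.5 to 0.7 and 68 students, a nominal 5% test operates at about 0.7% down to 0.04%. Power at a paired effect of 0.5 drops from about 0.98 to between 0.89 and 0.66. These sizes rest on the assumed correlation and on approximately normal total scores; the direction rests only on the correlation being positive. The paired t tests are not affected.

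**What to change.** In Data Analysis, replace the rank sum test with the Wilcoxon signed-rank test, applied to each student's posttest-minus-pretest difference, with the two records linked by the study ID.

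The article schedules analysis to be complete by May 2024 and was published in September 2024, so correcting the name is not enough on its own. The authors should also confirm that the related-samples procedure was the one used, and rerun any P value that came from the independent-samples procedure.

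The correction is one word. It needs no new data, no change of sample size and no other software; any rerun selects the related-samples option in the same package.
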